## Abstract

**Background:**

Children with attention-deficit/hyperactivity disorder (ADHD) suffer from attention deficits, motor hyperactivity, and impulsive behaviour. These impairments are experienced at home, at school, and with friends. Functional imaging studies show that ADHD behaviour and impairments in executive functions (EFs) are mirrored by aberrant neurophysiological functioning. Moreover, several studies show that ADHD behaviour, impairments in EFs, and a lack of self-control contribute to poor school performance. Non-pharmacological interventions such as neurofeedback training (NFT), for instance, aim at improving neurophysiological and neuropsychological functioning as well as behaviour. Consequently, NFT is expected to improve school performance, EFs, and self-control in children with ADHD. Generalization of acquired self-regulation skills from laboratory to real life is crucial for a transfer to everyday situations and is hypothesized to be facilitated via training using virtual reality (VR) environments. Consequently, experiencing NFT in VR is expected to yield greater effects than training in two dimensions (2D).

**Methods/design:**

Ninety children with a clinical diagnosis of ADHD will be included in the study. Participants may be medicated or unmedicated. After random assignation to one of three conditions, all participants receive 15 training sessions of either near-infrared spectroscopy (NIRS)-based NFT in VR, NIRS-based NFT in 2D, or electromyogram-based biofeedback training in VR. ADHD symptoms, self-control, EF, health-related quality of life, school performance, and motor activity measured via parent, teacher, and child reports or objectively will be assessed before and after the intervention and at a 6 months follow-up. Furthermore, we are interested in parents’ expectations about the training’s effects.

**Discussion:**

This is, to our knowledge, the first study investigating the efficacy of NFT for children with ADHD in a VR compared to a 2D environment. Furthermore, this study will contribute to the discussion about the efficacy and specific and unspecific effects of NFTs in children with ADHD. In addition to commonly assessed variables such as ADHD symptoms, NIRS and behavioural data obtained in EF measures, health-related quality of life, and parents’ expectations about the intervention’s effects, this study will investigate the effects on self-control, school performance, and motor activity.

**Trial registration:**

ClinicalTrials.gov, NCT02572180. Registered on 19 November 2015.

**Electronic supplementary material:**

The online version of this article (doi:10.1186/s13063-016-1769-3) contains supplementary material, which is available to authorized users.

## Background

Children with attention-deficit/hyperactivity disorder (ADHD) are inattentive, hyperactive, and impulsive [1]. They also experience difficulties in waiting for rewards, planning actions, and self-controlling in situations characterized by delay [2–4]. Affecting 5% of all children worldwide, ADHD is one of the most prevalent mental disorders in children [5].

### School performance in children with ADHD

The core symptoms of ADHD, namely inattention, hyperactivity, and impulsivity, are present in various settings, for instance, when working on tasks that require sustained attention or while doing homework. Hence, ADHD affects performance levels at home and at school [1]. Children with ADHD demonstrate lower school achievement as a consequence of ADHD symptoms and concomitant impairments in executive functioning (EF) when compared to children without ADHD [6]. In addition, children with ADHD are four to five times more likely to be in need of special educational services compared to children without ADHD [7]. Several studies support the notion that the ADHD symptomatology acts as a primary reason for educational underachievement [7–9]. Several studies also provide evidence that deficits in EF such as, for instance, working memory and processing speed, might be crucially involved in impaired school performance of children with ADHD (see, e.g. [10–13]). Consequently, treatment of ADHD in schoolchildren should aim at improving behaviour as well as self-control and EF to eventually improve school performance.

### Neurophysiological findings in children with ADHD

Behavioural characteristics of children with ADHD are mirrored by altered cortical and subcortical activity patterns that can be measured with brain imaging techniques such as electroencephalography (EEG) and functional near-infrared spectroscopy (fNIRS) [14–16]. In EEG studies, children with ADHD show not only an increased theta/beta ratio, but also a reduced contingent negative variation (CNV) (see, e.g. [14, 17–19]). With fNIRS, Ehlis and colleagues [16] were able to provide evidence for a reduced concentration of oxygenated haemoglobin (oxy-Hb) in the ventrolateral prefrontal cortex of adults with ADHD, compared to a healthy control group, during a working memory task. This finding was replicated in children with ADHD for the inferior prefrontal cortex during a Stroop colour-word task [15]. These deviations from normal brain activity constitute neurophysiological correlates of behavioural problems and impaired EF in patients with ADHD (see, e.g. [14, 16, 20, 21]). Consequently, we assume a treatment aiming at normalizing these deviant neurophysiological patterns to improve behaviour and EF in children with ADHD.

### Neurofeedback training (NFT) in children with ADHD

Neurofeedback training (NFT) sessions are interventions based on the above-mentioned neurophysiological findings. They aim at improving self-regulation on two levels: on a neurophysiological as well as on a cognitive behavioural level [22]. In NFT, brain activity is translated into simple visual or acoustic signals which are immediately fed back to the patient [23]. Depicting learning as a controlled, effortful, and explicit as well as implicit, automatic process that is influenced by cognitive-attributional variables such as motivation, allows patients to acquire techniques that allow them to self-regulate their brain activity [22]. Hence, NFT aims at facilitating phasic changes of brain activity and enhancing neurophysiological functioning [22]. In addition, NFT aims to improve self-regulation on cognitive behavioural levels; i.e. participants are required to concentrate, to sit still, to endure boredom, and not to react on impulse during the training sessions.

Studies examining the effects of EEG-based NFT show inconsistent results. For instance, Holtmann and Cortese and colleagues [24, 25] could not find evidence for an improvement of ADHD symptoms that was specifically related to the NFT itself. However, Arns and colleagues [26] found significant effects when comparing 15 studies in a meta-analysis. Furthermore, Marx and colleagues [27] showed in a pilot study that NIRS-based NFT in children with ADHD significantly reduced ADHD symptomatology after 12 training sessions. Extending beyond a mere influence of NFT on ADHD symptomatology, Meisel and colleagues [28] demonstrated that NFT significantly improved academic performance in children with ADHD. In contrast, stimulant medication could not be shown to effectively help schoolchildren in overcoming poor school performance, although it has a significant effect on improving behaviour [29]. However, further research is required to clarify the effects of NFT, especially NIRS-based NFT. Besides effects on ADHD symptoms, school performance, EF, EF-related frontal lobe activation, health-related quality of life (HRQoL), and self-control, the present study will investigate potential moderating influences of baseline ADHD symptoms, self-control, and IQ as well as training motivation. The effects of two NIRS-based NFT types (see below) will be compared to effects from an active control condition receiving an electromyogram (EMG)-based biofeedback training (BFT).

### Control conditions for NFT studies

In prior NFT research, different control conditions have been used to investigate the efficacy of NFTs. For instance, sham feedback has been implemented, but is criticized due to strong ethical concerns and participants’ poor compliance to treatment [30–33]. In the present study, an active control condition receiving an EMG-based BFT will be used to illustrate specific as well as unspecific effects of NIRS-based NFT. Looking at the effects of NFT and BFT, it is important to recall that NFT aims at improving self-regulation on two levels, neurophysiological as well as cognitive behavioural [22]. As illustrated below, the latter level is also targeted in BFT. In both NIRS-based NFT and EMG-based BFT, participants are expected to acquire self-regulation skills that allow the exertion of control over a specific endogenous parameter, for instance, prefrontal activity in the NFT and activity in the musculi supraspinatus in the EMG condition. In addition, participants learn to self-regulate behaviour such as being attentive, sitting still, not reacting on impulse, and enduring boredom. Consequently, we expect both NIRS-based NFT and EMG-based BFT to yield similar behavioural effects, as participants learn to self-regulate behaviour in both conditions. However, effects related to the acquisition of self-regulation skills related to the respective endogenous parameter are uniquely attributable to the parameter itself. As only NIRS-based NFT aims at normalizing aberrant brain activity, which is assumed to constitute a neurophysiological correlate of behavioural problems in children with ADHD [15], we consequently expect larger total effects from the NIRS-based NFT than from the EMG-based BFT.

### NFT in a virtual reality (VR) environment

To our knowledge, until now, no NFT study in children or adults with ADHD employing a virtual reality (VR) environment as a training setting has been conducted. However, from our perspective, there are several reasons suggesting that patients with ADHD can profit from training in a VR environment.

First, it is hypothesized that both the acquisition of self-regulation skills in the laboratory and the transfer to everyday life situations (e.g. a classroom setting) will be facilitated by training in a naturalistic VR environment. VR environments are often used in the treatment of mental disorders such as anxiety disorders and post-traumatic stress disorder, and were shown to be equally effective compared to therapies employing exposures to real-life situations [34]. Strong effects of therapies using naturalistic VR environments are attributed to the fact that various naturalistic stimuli, i.e. sounds, visual impressions, and haptic experiences, stimulate different sensory channels at once, thereby eliciting realistic psychological and behavioural responses [34]. Consequently, children with ADHD are expected to behave similarly inattentively, hyperactively, and impulsively in VR as well as in real-life classrooms. In NFT and BFT sessions, therapists may use these responses to work towards changes in behaviour by correcting inadequate, and by reinforcing appropriate behaviour, i.e. by training successful self-regulation of behaviour. Furthermore, aberrant psychological responses occurring in specific situations, for instance, an underactivation of prefrontal cortical areas in children with ADHD, are elicited by a naturalistic VR environment such as a VR classroom [34]. In NFT, but not in an EMG-based BFT, these inadequate responses are corrected as participants acquire self-regulation strategies that allow them to normalize their brain activity. Additionally, the effects of therapies employing naturalistic VR environments can be attributed to the high degree of realism that supports the transfer of skills acquired in the therapy or training to real-life situations, i.e. from a VR to a real-life classroom [34]. Consequently, we expect larger effects from NFT taking place in naturalistic VR environments than from training taking place in two-dimensional (2D) settings, as the acquisition and transfer of behavioural and psychological self-regulation skills are facilitated.

Second, after reviewing predictors and moderators of the efficacy of cognitive training, Keshavan and colleagues suggest that training motivation plays a major role [35]. This is in line with results presented by Käthner and colleagues, who provide evidence for a significant influence of motivation on task performance in the brain-computer interface [36]. The crucial role of training motivation in making cognitive training effective can be explained by findings that support the assumption that motivational state and positive mood facilitate prefrontal activation and consequently cognitive control, that is “the ability to select thoughts or actions in relation to internal goals” [37, 38]. In NFT for children with ADHD, both cognitive control and variability in prefrontal activity are essential, as participants are instructed to select thoughts that allow for a self-regulated increase or decrease of prefrontal activity. Consequently, NFT should aim at creating training settings that foster training motivation and positive mood. According to Keshavan and colleagues, intrinsic motivation in cognitive training can best be fostered by providing a “personalized context that links cognitive training to goals of everyday life” [35]. With the naturalistic VR classroom of the present study, a personalized context of everyday life is provided and should consequently foster cognitive control and prefrontal activation of the participants. Consequently, we expect NFT and BFT taking place in a naturalistic VR environment to yield larger effects than training in 2D. Furthermore, the effects of the training are expected to be moderated by the training motivation.

### Hypotheses

First, we hypothesize that NIRS-based NFT of the frontal lobe (dorsolateral prefrontal cortex (dlPFC) and EMG-based BFT improve ADHD symptoms, self-control, EF, HRQoL, school performance, and motor activity in children with ADHD independent of whether the training is conducted in 2D or VR. Second, we expect larger positive effects for NIRS-based NFT in 2D and VR than for EMG-based BFT in VR both at a post-test time point and at 6 months follow-up. Third, we expect the effects of NIRS-based NFT to be larger in the VR condition. Fourth, for NIRS-based NFT in 2D and VR, we expect an increase prefrontal in cortical activation during EF tasks at post-test and at 6 months follow-up.

## Methods/design

This manuscript as well as the trial it describes are in accordance with the Standard Protocol Items: Recommendations for Interventional Trials (SPIRIT) guidelines [39, 40]. See Additional file 1 for the SPIRIT checklist.

### Participants and recruitment

We will recruit approximately 90 participants with a clinical diagnosis of ADHD (any presentation) that is given based on the 5th edition of the *Diagnostic and Statistical Manual for Mental Disorders* [41] via medical offices of paediatricians, child and youth psychologists, and psychiatrists as well as offices of occupational therapists. Furthermore, we will recruit participants via the outpatient department of the Department of Child and Adolescent Psychiatry and Psychotherapy, University Hospital Tübingen, and local school psychologists. In addition, circular emails sent to members of the University of Tübingen, websites of the authors’ departments, local newspapers, and radio stations will announce the study. Information gained using the long version of the Conners 3 questionnaire for teachers and parents [42], the Strengths and Difficulties Questionnaire **(**SDQ-Deu) [43], and an interview with the parents are used to confirm diagnoses of ADHD. The training sessions will take place in the Department of Psychiatry and Psychotherapy at the University of Tübingen. See Table 1 for an overview of the eligibility criteria.

**Table 1 Tab1:** Eligibility criteria

Inclusion criteria	In school Grades 1–4 (age 6–10).
	Clinical diagnosis of ADHD combined, predominantly inattentive or predominantly hyperactive-impulsive presentation according to the Diagnostic and Statistical Manual of Mental Disorders, fifth edition (DSM-5)
	Written informed consent from parents/legal guardian
Exclusion criteria	IQ <70 as assessed with the Culture Fair Test (CFT) 1-R or the CFT 20-R [44, 45]
	Parent-reported diagnosis of the following: serious physical illness or chronic diseases such as pulmonary diseases, heart diseases, diabetes, hypertension, and rheumatic diseases; neurological disorders including stroke, multiple sclerosis, and epilepsy; indicated psychiatric disorders including obsessive-compulsive disorder, chronic tic disorders, Tourette’s syndrome, and suicidal behaviour
	Prior or current participation in neurofeedback training (NFT)/biofeedback training (BFT)
	Other psychotherapeutic treatment or any kind of attention training, also in the course of an ergotherapeutic treatment, while participating in the study

### Randomization

The design involves three conditions (*n* = 30 per condition; *N* = 90) to which recruited children will be assigned randomly upon confirmation of all inclusion criteria. One of the principal investigators of this study who is only occasionally involved in training and testing participants executes the randomization. A block randomization procedure is applied, and balancing the conditions for age, gender, and ADHD medication stratifies the randomization.

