#### Time points of assessments

The first assessment (t_−1_) takes place in order to check for all relevant inclusion and exclusion criteria. Zero to two weeks before the first training session, two baseline measurements of all relevant variables take place (t_0_). Medication washout is required for one of the two test sessions in which neuropsychological and neurophysiological measurements are applied. For an overview of the variables assessed under medication washout, see Fig. 4. After eight training sessions, ADHD symptoms are assessed in a midway test (t_1_). Zero to two weeks after the last training session, a post-test measurement of all relevant variables, again under medication washout for one of the two sessions, takes place (t_2_). Six months after the last training session, all relevant variables are again assessed in a follow-up test (t_3_).

For an overview of the tests, questionnaires, and methods employed at different time points in the study, see Fig. 4, which was designed in accordance with the standard protocol items for clinical trials [39, 40].

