#### Primary outcome measures

Mean group scores of every condition will be calculated for all primary outcome measures. The C3-P and C3-T [42] assess ADHD symptoms as rated by parents and teachers at pre- (t_0_), midway (t_1_), post- (t_2_), and follow-up test (t_3_), hence allowing us to assess changes within and between conditions from pre- to midway, from pre- to post-, and from pre- to follow-up test. Furthermore, at pre- (t_0_), post- (t_2_), and follow-up test (t_3_), brain activity, i.e. the mean levels of oxy-Hb and deoxy-Hb at various channels across different cortical areas, is assessed using fNIRS data as well as EEG data from the *n*-back task assessing working memory, the Go/NoGo task assessing response inhibition, and the VFT assessing general brain activity. Consequently, changes within and between conditions in brain activity from pre- to post-, and from pre- to follow-up test can be assessed. In addition, behavioural data (i.e. mean reaction times, mean reaction time variability (*SD*), and the mean total number of commission and omission errors) are obtained from the *n*-back task and the Go/NoGo task at pre- (t_0_), post- (t_2_), and follow-up test (t_3_), hence allowing us to assess changes from pre- to post-, and from pre- to follow-up test within and between conditions.

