#### Secondary outcome measures

Mean group scores of every condition will be calculated for all secondary measures. Secondary outcome measures assess diverse constructs at pre-test (t_0_), post-test (t_2_), and follow-up test (t_3_), hence allowing us to compare changes within and between conditions from pre- to post-test and from pre- to follow-up test. Children’s HRQoL is assessed using the KINDL-R questionnaires for parents and children. Parents’ satisfaction with as well as their expectations about the intervention’s effects are assessed using the FERT questionnaire [57]. Children’s mathematics, reading, and writing skills are assessed using the LVD-M 2–4 [68] and the SLRT-II [79]. Children’s self-control and academic self-efficacy are assessed using the SCS-K-D and a scale by Schwarzer and colleagues [54] in both a version for parents and one for their children. Executive functioning is furthermore assessed using a digit span task [64] (verbal working memory), the Corsi Block Tapping Task [62] (visuo-spatial working memory), and the BRIEF [56], a questionnaire handed out to parents and teachers. Sustained attention is assessed using the Conner’s Continuous Performance Test [61, 67], and response inhibition is assessed using the Stop-Signal Task [80]. General cognitive ability is assessed using the matrix span task [64]. Moreover, activity data are collected with actigraphs measuring acceleration on the vertical, horizontal, and perpendicular axes with a range of −6 to +6 g (g = gravitational force). Heart rate variability, as calculated from the ECG, as well as the motivation for every training session, as assessed with a self-report questionnaire for the children, serve as secondary outcome measures.

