Children with ADHD experience poor school performance [6–8] as well as a core deficit in self-control [3], that is, “the deliberate, conscious, effortful subset of self-regulation” [82]. However, aspects often neglected in prior studies include the effects of NFT and BFT on self-control and school performance. Depicting NFT and BFT as interventions that train the exertion of self-regulation in two domains, namely self-regulating an endogenous parameter and self-regulation of behaviour, it seems plausible to expect effects on and to assess self-control while investigating effects on the self-regulation of brain activity and behaviour. Furthermore, as poor school performance is related to difficulties in behaviour, EF, and self-control [8], and both NFT and BFT have been shown to improve behaviour and EF (e.g. [83, 84]), we should expect all three interventions administered in this study to improve school performance. Hence, it is vital to assess the effects of a NIRS-based NFT and an EMG-based BFT on school performance.

The present study is limited in that participants, parents, and the trainers administering the intervention are not blinded — even though an official debriefing of parents and children as well as communication of individual results will only take place after finishing the study, hence, after the follow-up test is completed. First, participants, parents, and trainers are not blinded due to time constraints that make it impossible to use both the NIRS machine and the EMG equipment simultaneously. Second, participants either wear or do not wear the HMD, and hence they will know whether it is the 2D or VR condition they belong to. Third, as measurements during training sessions require constant observation of the data being recorded, it is impossible to blind trainers for the kind of intervention administered. However, participants, parents, and trainers are informed that every participant receives a potent intervention. Hence, we hope that bias is reduced to a minimum.

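### As written, children are randomised before the t0 baseline and no step withholds the arm until t0 is complete, so parent- and child-reported pre scores in this open trial may be given with the arm known

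*Protocol article*

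**What the plan says.** All references are to the protocol article.

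- **Randomization:** "recruited children will be assigned randomly upon confirmation of all inclusion criteria". The factors balanced are age, gender and ADHD medication. The draw is made by a principal investigator who takes some part, though only occasionally, in training and testing.
- **Time points of assessments:** the first assessment, t-1, "takes place in order to check for all relevant inclusion and exclusion criteria". Baseline, t0, comes next: "Zero to two weeks before the first training session, two baseline measurements of all relevant variables take place". One of the two t0 sessions is held under medication washout.
- **Discussion (limitations):** "participants, parents, and the trainers administering the intervention are not blinded". One reason given is that "participants either wear or do not wear the HMD, and hence they will know whether it is the 2D or VR condition they belong to". The mitigation offered is that "participants, parents, and trainers are informed that every participant receives a potent intervention", with debriefing and individual results held back until after follow-up.
- **Primary outcome measures:** "The C3-P and C3-T [42] assess ADHD symptoms as rated by parents and teachers at pre", midway, post and follow-up, and effects are read as change from the pre-test. Secondary outcomes likewise serve to "compare changes within and between conditions from pre- to post-test and from pre- to follow-up test".
- **Statistical evaluation of the results:** repeated measures ANOVA is planned for all outcomes. Once a (neuro-)psychological test is missing, that child's later results on the test are dropped as well.

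**The concern.** A baseline protects a comparison of change only if it cannot be affected by the allocation. Here the draw is tied to the eligibility check, which precedes t0, and nothing in the article keeps the result from families until t0 is finished. A parent who knows whether the child will receive VR or 2D training, or brain or muscle training, may rate the child differently at t0. The difference then enters every pre-to-later contrast of that rating as an apparent arm effect.

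A second consequence does not depend on when the arm is disclosed. A child who leaves or misses a test between the draw and t0 has been randomised but has no pre value. For the tests, the missing-data rule then removes the later values too.

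**Working it through.** **Order of the steps.** The draw follows confirmation of the inclusion criteria (Randomization). Those criteria are checked at t-1, and t0 comes later, within two weeks before session 1 (Time points of assessments). The draw therefore falls between t-1 and t0. Nothing in the text requires this order, because age, gender and medication status are not t0 scores.

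**Which pre scores are exposed.**

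| t0 measure | Source | Exposure if the arm is known |
|---|---|---|
| Conners 3 parent form | Parent, listed as unblinded | Exposed, unless the diagnostic rating made before allocation serves as t0 |
| BRIEF parent form, KINDL-R, self-control, FERT expectations | Parent and/or child, listed as unblinded | Exposed |
| Conners 3 and BRIEF teacher forms | Teacher, not listed as unblinded | Less exposed |
| NIRS, EEG, computerised tasks | Instrument | Less exposed; effort or tester effects remain possible |

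**The plan's own figures.** The point rests on none of them and changes none. The total of 84 reproduces as a group-by-time test with ES .35 read as d, so f = 0.175. Then λ = N·f²·m/(1−ρ) = 84 × 0.030625 × 2/0.5 = 10.29, and power is 0.812.

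**Illustration of size.** From the plan: 30 per arm and a correlation of .5 between repeated measures. Assumed, and not in the documents: no training effect, a shift b at t0 in one arm, later scores unaffected, one pairwise contrast, two-sided 5%, normal approximation.

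- Change score: variance 2(1−0.5) = 1 SD²; SE of the arm difference √(2/30) = 0.258 SD; bias b.
- Baseline as covariate: residual SD √(1−0.25) = 0.866; SE 0.866 × 0.258 = 0.224 SD; bias 0.5b.
- Rejection rate: P(Z > 1.96 − bias/SE) + P(Z < −1.96 − bias/SE).

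| b (SD) | Change score | Baseline as covariate |
|---|---|---|
| 0.1 | 6.7% | 5.6% |
| 0.2 | 12.1% | 7.3% |
| 0.3 | 21.3% | 10.3% |

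For b = 0.2 on the change score, bias/SE = 0.775, giving P(Z > 1.185) + P(Z < −2.735) = 0.118 + 0.003 = 0.121.

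If the same shift b also appears at the later visit, the change-score bias is b − b = 0.

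**The case against.** **Randomised is not the same as told.** The article does not say when families learn the arm. Its reasons for not blinding (NIRS or EMG equipment, the head-mounted display, trainers watching the recording) all arise in training sessions, which follow t0. This stands. A reader might infer that parents and children already know the arm at t0, but the text does not establish it.

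**The parent Conners may predate the draw.** Under Participants and recruitment, the long Conners 3 from parents and teachers helps confirm the diagnosis, which is an inclusion criterion. If that rating is the t0 value, this baseline is safe. The outcome section labels the pre score t0 and does not settle the matter. The flow chart and the schedule figure, which might, are not visible here.

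**Not every change is affected.** A reader might extend the concern to all outcomes. Teachers are not listed as unblinded, and the NIRS, EEG and computerised measures are not ratings. FERT is also a debatable example, since it asks about the intervention the child is to receive. The narrower scope stands.

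**Differential bias is not shown.** All three arms are active and families are told so, and a constant rating shift would cancel. Both points limit the likely size. Neither is a safeguard, because constancy of the shift cannot be checked.

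**An article may leave disclosure to the full protocol.** That is fair for the disclosure date alone. The order of draw and baseline, however, is stated in the text, and it is the order that creates the opening and the loss after randomisation.

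**Conclusion.** The point holds in limited form. Taken together, the Randomization and time-points sections place allocation before t0 in an open trial, with no stated step that withholds the arm. Parent- and child-reported pre scores may therefore be influenced by knowledge of the arm. The documents do not show that they are, nor that all outcomes are at risk.

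No size can be taken from the documents. The 12–21% applies to one pairwise contrast under an assumed shift of 0.2–0.3 SD confined to t0. Baseline adjustment would reduce it to about 7–10% without removing it. It should not be read as the trial's expected error rate.

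Loss of children between the draw and t0 follows from the stated order and the missing-test rule, whatever the disclosure date. Its extent is also not given.

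**What to change.** Amend the Randomization section to say that children are randomised after all t0 measurements and questionnaires are complete. If scheduling needs an earlier draw, state that the allocation is kept from families, trainers and testers until then. That second option closes the rating route but not the loss between draw and t0. State also which Conners rating serves as the t0 value.

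The trial is ongoing, so for children already enrolled, record whether t0 preceded knowledge of the arm, and repeat the primary analysis as a sensitivity analysis in those for whom it did.

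The cost is a short amendment reordering two existing steps, with no extra visit, staff or test. Trainers would learn the arm somewhat later and book equipment accordingly. The change secures the baseline only; open rating at later visits remains the limitation that the article already acknowledges.
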